### Study design

A quasi-experimental design with a comparison group will be used for the study. The preceding formative work investigated the knowledge, attitudes and practices regarding mental health issues and resilience-building in the population, and the likely acceptability, appropriateness and feasibility of the planned screening and referral intervention using focus group discussions (FGDs) and in-depth interviews (IDIs). Findings from the formative work were then incorporated into the development of the training materials for LHWs and health facility staff.

To evaluate the feasibility and effectiveness of the screening and referral intervention, LHWs will be trained to screen WRA through the brief two-item Generalized Anxiety Disorder scale (GAD-2)^16^ and brief two-item Patient Health Questionnaire (PHQ-2),^17^ and administer awareness-raising and resilience-building sessions along with appropriate referral to Basic Health Unit (BHU). Facility staff present within BHU will be trained to confirm the screening using the 7-item Generalized Anxiety Disorder scale (GAD-7)^18^ and the 9-item Patient Health Questionnaire (PHQ-9),^19^ provide counselling and refer severe cases to specialists at tertiary care facilities.

The study duration is January to December 2025 with the initial few months focusing on the formative phase followed by the actual intervention. This trial is registered at clinicaltrials.gov with number NCT06756165.

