### Study site

This study will be conducted in the flood-affected areas of Dadu district in Sindh province, Pakistan. Dadu is located west of the Indus River, approximately 160 km north-northwest of Hyderabad. It was one of the worst-affected areas during the flooding in 2022, with an immense increase in water-borne illnesses and loss of shelter, basic resources and agricultural livelihoods.^20^

The district of Dadu is administratively subdivided into four Talukas: Dadu, Johi, Khairpur Nathan Shah and Mehar. The study will take place specifically in Taluka Khairpur Nathan Shah, where 8 flood-affected Union Councils (UCs) were purposely chosen as they were the most severely affected and assigned into two groups: 4 UCs for the intervention group (Gozo, Burira, Chor Qambar and Kande-Chukhi) located on the left side of the Taluka Headquarters and 4 UCs for the control group (Dhani Bux Bughio, Parya, Thalo and Sindhi Butera) located on the right side to maintain distance and avoid contamination. Each UC in both arms has one BHU and a 24/7 Maternal, Newborn and Child Health (MNCH) Center.

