### Sample Size

The sample size was calculated based on an estimated anxiety prevalence of 25.6%. To detect a 20% relative difference in prevalence between study arms with 90% power and a 5% level of significance, estimated intracluster correlation coefficient (ICC) of 0.0033 and an anticipated attrition rate of 10%, a total of 20 clusters per arm with 105 women per cluster (ie, 2100 women per arm) will be required. The prevalence of anxiety is assumed to vary by ±5 percentage points between clusters. The coefficient of variation (CV) was estimated based on this range, and the ICC was then derived using the CV formula.^21 22^

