### Data analysis

#### Quantitative component

The data collected and stored on the server will be exported to Stata version 18 for analysis. Data will be cleaned, and errors will be rectified under the guidance of the study investigators. Descriptive statistics will be presented: mean and SD, or median with IQRs for continuous variables, depending on the data distribution, and frequency distributions for categorical variables. Feasibility, acceptability and appropriateness of the intervention were assessed through proportions with 95% CIs. For mental health outcomes, difference-in-difference (DID) analyses will be conducted through logistic regression analysis, assuming parallel trends i.e., intervention and control arms had parallel trends in the outcomes before the intervention was introduced. The model incorporates an interaction term for time and intervention effect. The coefficient of the interaction term serves as DID estimate. Further, to address potential confounding, the DID will be adjusted for imbalanced factors at baseline. In addition, the model will also include covariates that are known to affect the outcome such as age, education, marital status, parity, socioeconomic status and trauma. For missing data on variables, the plan will be not to impute but treat this as missing and perform complete case analysis. All analysis will be adjusted to account for the cluster randomised design.

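### The analysis is tied to a cluster randomised design that the study does not have, and the plan's only cluster count (20 per arm) is not the allocated unit (4 Union Councils per arm)

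*Protocol article*

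**What the plan says.** The last sentence of the Quantitative component under Data analysis reads "All analysis will be adjusted to account for the cluster randomised design". It names no cluster unit, variance estimator or reference distribution.

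The Study design section says "A quasi-experimental design with a comparison group will be used for the study", and the abstract agrees. Under Study site, "8 flood-affected Union Councils (UCs) were purposely chosen as they were the most severely affected and assigned into two groups". The intervention arm is "4 UCs for the intervention group (Gozo, Burira, Chor Qambar and Kande-Chukhi) located on the left side of the Taluka Headquarters"; the four control UCs are "located on the right side to maintain distance and avoid contamination". No random step is described anywhere in the article.

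The Sample Size section plans "To detect a 20% relative difference in prevalence between study arms with 90% power and a 5% level of significance", with 20 clusters per arm of 105 women each. It does not say what a cluster is. Hiring and training mentions 20 Lady Health Workers (LHWs) in the intervention arm, so the clusters may be LHW areas, but the article does not make that link.

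The effectiveness analysis is a logistic difference-in-difference (DID) that assumes parallel trends. Objectives and Outcomes make effectiveness secondary; the primary outcomes are feasibility proportions.

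**The concern.** Two things are wrong with the sentence as it stands.

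First, it misnames the design. Arm coincides completely with side of the Taluka, so any difference in trend between the two areas is inseparable from the intervention effect. The comparison rests on parallel trends. Table 2 of the article schedules a single pre-intervention survey, so the study's own data cannot test that assumption. No clustering adjustment removes this.

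Second, it leaves open what the adjustment is for. The unit that was assigned, and that shares one Basic Health Unit, is the UC: four per arm, eight in all. A reader looking for the cluster finds only 20 per arm. Adjusting at that level treats sub-areas of one UC as independent. Adjusting at UC level with ordinary robust errors relies on large-sample theory with eight clusters. Either route can give intervals that are too narrow for the only between-arm comparison in the study. This problem comes from the small number of allocated units; confounding by area is separate and comes from the non-random assignment.

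**Working it through.** **1. The plan's own figure.** Inputs from Sample Size: prevalence 25.6%, 20% relative difference (so 20.48%), 90% power, 5% significance (taken as two-sided), ICC 0.0033, attrition 10%, 105 women per cluster.
- ICC: reading ±5 points as two SDs gives SD 0.025 and CV = 0.025/0.256 = 0.0977. Then ICC = CV² × p/(1 − p) = 0.0033, as stated.
- Women per arm without clustering: 1420. Design effect 1 + 104 × 0.0033 = 1.343, giving 1907. Dividing by 0.9 gives about 2120; multiplying by 1.1 gives about 2099. Stated: 2100.

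The figure reproduces, but only with 20 independent clusters per arm.

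**2. Robust standard error on the eight UCs.** Let SS be the pooled within-arm sum of squares of the UC changes, four per arm.
- Unbiased variance of the arm difference: (SS/6) × (1/4 + 1/4) = SS/12.
- Cluster-robust variance with the usual factor: (8/7) × SS/16 = SS/14.
- Normal reference: P(|t₆| > 1.960 × √(12/14)) = P(|t₆| > 1.815) = 0.120.
- t on 7 df: P(|t₆| > 2.365 × √(12/14)) = P(|t₆| > 2.189) = 0.071.
- Unbiased variance with t on 6 df (critical value 2.447): 0.050.

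**3. Adjustment at the 20-per-arm level.** Assumptions: five sub-clusters per UC, 94.5 women each after attrition (105 × 0.9), within-woman correlation r = 0.3, normal reference.
- Sampling variance of one sub-cluster's change: v = 2 × 0.256 × 0.744 × (1 − 0.3)/94.5 = 0.00282.
- With SD s for UC-level change, the true variance of an arm mean is s²/4 + v/20. The sub-cluster calculation has expectation of about (v + 0.79 s²)/20, where 0.79 = 0.75 × 20/19, so it misses most of the s² term.

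Type I error of the nominal 5% test, by simulation with 200,000 runs per row:

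| SD of UC change (assumed) | Sub-cluster adjustment | UC-level t, 6 df |
|---|---|---|
| 0 points | 6% | 5% |
| 1 point | 8% | 5% |
| 2 points | 13% | 5% |
| 2.5 points | 16% | 5% |
| 5 points | 29% | 5% |

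A separate simulation of the logistic DID, with independent samples at each survey, agrees in direction. Coverage of nominal 95% intervals was about 88% for the UC-level robust error with a normal reference. At sub-cluster level it was 94%, 90% and 81% for UC-by-period SDs of 0, 1.25 and 2.5 points. It was about 95% for the UC-level t.

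**4. Power with the UC as cluster.** Simple endline comparison, stated ICC, 5 × 94.5 = 472.5 women per UC:
- Design effect 1 + 471.5 × 0.0033 = 2.556.
- Standard error √[(0.256 × 0.744 + 0.2048 × 0.7952) × 2.556/(4 × 472.5)] = 0.0219.
- Difference over standard error: 0.0512/0.0219 = 2.34.
- Power is about 65% with a normal reference and 50% with t on 6 df, against the stated 90%.

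**The case against.** The strongest reply is that the article commits to no faulty method. It names no cluster unit, estimator or reference distribution, and an article may leave those to a fuller document. A small-sample correction specified there would remove the UC-level problem. This stands: the error rates show what follows from particular readings, not what the plan prescribes.

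Three stronger readings are tempting, and the article does not support them.
- *The clusters are LHW areas.* The match with 20 LHWs is suggestive, but those workers are mentioned for the intervention arm only and clusters are never defined.
- *The plan's ±5 points implies an SD of 2.5 points for UC changes.* That figure describes prevalence levels between the plan's own clusters. A DID removes stable differences in level, and the article gives no figure for variation in change. The range must therefore start at zero, where the cost is about 6% against 5%.
- *The authors claim the protection of randomisation.* The same paragraph states the parallel-trends assumption and adjusts for baseline imbalance to deal with confounding, so the analysis is visibly built for a non-randomised study.

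What the reply does not rescue is the sentence itself. It describes a design that the rest of the article contradicts, and the one cluster count a reader could apply to it is not the allocated unit.

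**Conclusion.** The point holds. The contradiction is certain and needs no calculation. The effect on inference is conditional: about 6% to 16% type I error for adjustment at the 20-per-arm level as the assumed SD of UC change goes from 0 to 2.5 points (r = 0.3, five sub-clusters per UC); about 12% or 7% for a robust error on eight UCs with a normal or t₇ reference; and 5% for a UC-level t on 6 df. Because the affected result is the secondary objective, and the primary feasibility proportions involve no between-arm test, this should be fixed but does not undermine the study's main purpose.

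**What to change.** Replace the sentence with: *Analyses account for the non-randomised allocation of 8 UCs; the UC is the cluster.* Define the 20 clusters per arm in the Sample Size section and say how they sit within UCs.

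Base inference for the effectiveness DID on a few-cluster method at UC level. One option is covariate-adjusted UC-level changes compared with a t reference on 6 df; state whether this replaces or supplements the logistic interaction coefficient now named as the DID estimate. The other is a wild cluster bootstrap at UC level, which keeps that coefficient.

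State that arm is fully confounded with side of the Taluka and that the result rests on parallel trends, which one pre-intervention survey cannot test. A permutation over the 70 possible four-against-four splits (smallest two-sided p = 2/70 = 0.029) may be shown as a descriptive sensitivity check only, since it has no randomisation basis here.

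No new data are needed. The price is wider intervals (2.447/1.960, about 25% from the critical value alone) and an open statement that power is below 90%: about 50% in the simple endline calculation above.

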#### Qualitative component

For the qualitative phase, thematic content analysis will be employed to systematically analyse data from FGDs and IDIs, identifying key themes and patterns that provide deeper insights into the intervention’s effectiveness, barriers and facilitators.

## Ethics and dissemination

### Ethical considerations

The study acquired ethical approval from the Ethical Review Committee at Aga Khan University (2024-10475-30776) and the National Bioethics Committee (4-87/NBC-1158/23/481) in Islamabad. The Ethics Review Committee (ERC) and health department will be informed of any modifications made to the protocol of the trial. Approval was obtained from relevant provincial authorities involved. The trial will adhere to the ethical principles of autonomy, anonymity, confidentiality, equity and respect. All eligible participants will be provided with informed consent, details regarding the purpose and procedure of the study, and the right to withdraw at any time. Collaboration will be maintained with the Sindh Lady Workers Programme and the District Health Department. Community engagement events will be conducted regularly to address concerns and encourage participation, with serious issues resolved through the community Jirga system. Severe cases of anxiety and depression will be referred to tertiary care with one-time transport provided by the study team. Coordination with tertiary care staff is in place to ensure seamless and prioritised care for referred individuals. A distress protocol will be established to support any participant or data collector experiencing any form of psychological distress due to the content of the study.

### Data management and dissemination

Data will be anonymised and securely stored, with protection protocols in place. The de-identified data will be shared at reasonable request and approval from the institute and the funding authority. The methods and outcomes of the study will be published in peer-reviewed journals. Dissemination of the results of the trial will occur after its completion to stakeholders, participants and the public.

## Discussion

Climate change-related disasters have become an alarming threat to the physiological and psychological health of individuals across the world. Worsened by climate change, floods have made people more susceptible to a variety of illnesses and financial crises.^26 27^ Additionally, low-middle income countries are already at a high risk of mental health issues due to the scarcity of resources and necessities including provision of mental health services.^28^ Coupled with the catastrophic floods of 2022 in Pakistan’s context, there have been a myriad of common mental health disorders significantly increasing in these affected areas.^27^

A protective factor which can combat the negative impact of floods and natural disasters on the mental health of those affected is social support.^29 30^ A study in Punjab’s flood-affected areas noted that higher social support was associated with lower levels of anxiety, stress and depression.^26^ Consequently, in this trial, community interventions will be incorporated to build climate change resilience and spread awareness regarding mental health among the flood-affected areas of Sindh. The focus of the study remains on women of reproductive age as they seem to be the most susceptible to the negative impact of floods.^27^ Even as per the findings of the formative phase of this trial, women suffered due to the absence of security, privacy and basic healthcare required, especially during pregnancy.

This contextually grounded, evidence-based intervention addresses the urgent and growing mental health needs of WRA in Pakistan’s climate-vulnerable regions. By embedding mental health services within the trusted LHW network and aligning with existing primary care structures, this initiative offers a sustainable and scalable solution if proven to be effective. It aims not only to alleviate psychological distress but also to foster resilience, restore agency and promote well-being in communities facing intersecting challenges of environmental stress and socioeconomic adversity.
